### Choice of open-label design

The open-label design was chosen for several reasons, the main being that in case of a blinded trial, the need for un-blinding would have been too frequent. Indeed, some of the previous studies showed that during the active phase of labor, 30 to 40% of the women with a discontinued administration of oxytocin required a re-start of oxytocin after a two-hour arrest of labor [14, 15]. Another situation requiring to un-blind the randomization group is in case of non-reassuring fetal heart rate which was the case in up to 8% of the women in Saccones’ metanalysis [12]. Indeed, in the context of non-reassuring fetal heart rate (FHR) it is important for the obstetrician to know the treatment group in order to stop the oxytocin infusion to reduce uterine contractility.

The choice of this design was discussed several times on the GROG’s meetings and the final decision was to choose an open-label design. The advantages are those described above, and the bias related to the open label design will be low considering that the primary endpoint is a composite variable of objective criterions.

Apart from oxytocin administration the labor management does not differ between the two groups. The condition to re-start oxytocin in the experimental group is well described, i.e. 2 h of labor arrest (no progression of the cervical dilation and no progression of the fetal head).

### Power calculation

A prospective population-based cohort study was conducted in France in 2015 assessing French practices of induction of labor, MEDIP (MEthodes de Déclenchement et Issues Périnatales) [19]. In this study, data on oxytocin use and neonatal outcomes is available. In the French MEDIP cohort, among women receiving oxytocin under standard care (as in our control group), 8% of neonates had at least one criterion of the primary endpoint of STOPOXY trial.

We hypothesize a decrease from 8% with standard care (i.e. control group) to 5% with discontinuation of oxytocin (i.e. experimental group). Assuming this decrease, we need a sample size of 1125 women in each group, for a power of 80% and an alpha risk of 5% with the use of a bilateral test. Because some women could be included and randomized, but never reach 6 cm of cervical dilation, and thus not receive the intervention, we plan to include 10% more women. We suppose that this number will correspond to the number of women having a cesarean delivery before starting the intervention, i.e. before 6 cm. Therefore, to reach statistical significance, we would like to include 2475 women in our trial.

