**Methods:**

STOPOXY is a multicenter, randomized, open-label, controlled trial conducted in 20 maternity units in France. The first participant was recruited January 17th 2020. The trial includes women with a live term (≥37 weeks) singleton, in cephalic presentation, receiving oxytocin before 4 cm, after an induced or spontaneous labor. Women aged < 18 years, with a lack of social security coverage, a scarred uterus, a multiple pregnancy, a fetal congenital malformation, a growth retardation <3rd percentile or an abnormal fetal heart rate at randomization are excluded. Women are randomized before 6 cm when oxytocin is either continued or discontinued. Randomization is stratified by center and parity. The primary outcome, neonatal morbidity is assessed using a composite variable defined by an umbilical arterial pH at birth < 7.10 and/or a base excess > 10 mmol/L and/or umbilical arterial lactates> 7 mmol/L and/or a 5 min Apgar score < 7 and/or admission in neonatal intensive care unit. The primary outcome will be compared between the two groups using a chi-square test with a *p*-value of 0.05. Secondary outcomes include neonatal complications, duration of active phase, mode of delivery, fetal and maternal complications during labor and delivery, including cesarean delivery rate and postpartum hemorrhage, and birth experience. We aim at including 2475 women based on a reduction in neonatal morbidity from 8% in the control group to 5% in the experimental group, with a power of 80% and an alpha risk of 5%.

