#### Analysis of the primary endpoint

The analysis of the primary endpoint will estimate the effect of discontinuous administration of oxytocin on neonatal morbidity defined by a composite variable. All women included and randomized in the study will be included in the analysis which will be an intent-to-treat analysis. The percentage of neonates with morbidity using the composite criteria will be compared between the two groups: discontinuous oxytocin or continuous oxytocin by a chi-square test.

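### The 10% added for women who never reach 6 cm does not preserve 80% power, because the intent-to-treat analysis keeps them: power at 2475 is about 77–78%

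*Protocol article*

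**What the plan says.** All references are to the protocol article.

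- **Power calculation.** The control rate comes from a French cohort in which, among women given oxytocin under standard care, "8% of neonates had at least one criterion of the primary endpoint of STOPOXY trial". The trial assumes a fall to 5% and asks for 1125 women per group at 80% power and 5% alpha, "with the use of a bilateral test".
- **Same section, the inflation.** The extra women are for those who, once randomized, might "never reach 6 cm of cervical dilation, and thus not receive the intervention, we plan to include 10% more women". The text then ties the size of the allowance to early cesareans: "We suppose that this number will correspond to the number of women having a cesarean delivery before starting the intervention, i.e. before 6 cm". The total becomes 2475.
- **Oxytocin infusion protocol and randomization.** Women are randomized 1:1 in the latent phase, before 6 cm. The two strategies differ only from 6 cm.
- **Analysis of the primary endpoint.** "All women included and randomized in the study will be included in the analysis which will be an intent-to-treat analysis". The test is a chi-square test, with no mention of a continuity correction. Under Planned analysis, the per-protocol analysis is additional.
- **Abstract, Methods.** "We aim at including 2475 women based on a reduction in neonatal morbidity from 8% in the control group to 5% in the experimental group", again at 80% power.

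**The concern.** The sample size and the primary analysis treat the same women differently. The 10% is a replacement allowance: it restores the number of women in whom the strategies can differ. It would restore power if the others were removed from the analysis, but they are not. A woman delivered by cesarean before 6 cm has had the same allocated care in either arm, so she adds to both denominators and nothing to the difference.

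When a share f of each arm has no contrast, the difference shrinks by the factor (1 − f). The required sample size then grows by roughly 1/(1 − f)², about 23% at f = 10%, rather than by 10%.

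What is at stake is how the result is read. The Background faults earlier trials for low power, and the Discussion presents adequate power as this trial's advantage. A null result would be judged against a power figure that the primary analysis does not have.

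**Working it through.** **Inputs**
- From Power calculation: 8% and 5%, two-sided 5% (z = 1.960), 80% power (z = 0.842), 1125 per group, 2475 in total. With 1:1 allocation that is 1237.5 per arm.
- Share never reaching 6 cm (f): read literally, the added women are 2475 − 2250 = 225, and 225/2475 = 9.1%. Read as a rate, f = 10%.
- Assumption: morbidity risk q among women who never reach 6 cm, equal in both arms. The protocol gives no figure. Base case 8%, varied from 4% to 16%.

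**1. The plan's own figures**

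Pooled formula: n = [1.960√(2·0.065·0.935) + 0.842√(0.08·0.92 + 0.05·0.95)]² / 0.03² = (0.6833 + 0.2929)² / 0.0009 = 1059 per group.

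With continuity correction: (n/4)·[1 + √(1 + 4/(n·0.03))]² = 1124.5, so 1125. This matches the stated figure exactly. Then 2250 × 1.10 = 2475, also exact.

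**2. Difference under intent-to-treat, q = 8%**

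Experimental-arm rate = 0.05(1 − f) + 0.08f.
- f = 9.1%: 5.27%, a difference of 2.73 points.
- f = 10%: 5.30%, a difference of 2.70 points.

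**3. Power at 1237.5 per arm**

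Power = Φ{[d√n − 1.960√(2p̄(1 − p̄))] / √(p₁(1 − p₁) + p₂(1 − p₂))}.
- f = 9.1%: (0.9594 − 0.6900)/0.3515 = 0.767, power 77.8%.
- f = 10%: (0.9498 − 0.6906)/0.3518 = 0.737, power 76.9%.

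Inverting the continuity correction turns 1237.5 into about 1165 uncorrected women per arm, which gives 75.4% and 74.4%. Exact binomial enumeration at 1237 per arm agrees: 78.2% and 77.3% for the plain test, 75.6% and 74.7% with correction.

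**4. Sensitivity**

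| f | q | Arm rates | Plain chi-square | Corrected |
|---|---|---|---|---|
| 5% | 8% | 8.0% vs 5.15% | 81.6% | 79.4% |
| 9.1% | 8% | 8.0% vs 5.27% | 77.8% | 75.4% |
| 10% | 4% | 7.6% vs 4.9% | 79.3% | 76.8% |
| 10% | 8% | 8.0% vs 5.3% | 76.9% | 74.4% |
| 10% | 16% | 8.8% vs 6.1% | 72.5% | 69.9% |
| 15% | 8% | 8.0% vs 5.45% | 71.7% | 68.9% |

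At q = 8%, the plain test reaches 80% only if f is about 7% or less.

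**5. Size needed for 80% in all randomized women, q = 8%**
- f = 9.1%: 2614 in total (plain) or 2758 (corrected).
- f = 10%: 2672 or 2818.

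**6. Where the 80% does hold**

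On the literal reading, 2475 − 225 leaves 1125 per arm who reach 6 cm. At 8% versus 5%, power there is 80.0% (corrected) or 82.3% (plain). The stated power therefore describes this group.

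**The case against.** **The 8% versus 5% may already be the effect in all randomized women.** The cohort figure is for women given oxytocin, with no stated restriction to those who reached 6 cm, and the Abstract links 2475 directly to 8% versus 5%. On that reading, power at 2475 is 85.7% (plain) or 83.8% (corrected). But then no inflation would be needed, whereas the plan adds 10% precisely because some women do not receive the intervention. That stated reason is hard to square with this reading.

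**The 74–75% figure is not the power of the planned test.** This stands. The article names no sample-size formula; the continuity-corrected one is inferred from the match to 1125. The planned test is a chi-square test with no stated correction. Under the plain test 1125 per group already gives 82.3%, which absorbs part of the dilution. A reader might take 74% as the protocol's own figure; the document does not support that.

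**The size rests on unstated inputs.** This also stands. The 10% is a supposition, and q is not given. The least favourable rows raise the control rate above the cohort's 8%. If the control arm is held at 8% with a 3-point effect in women who reach 6 cm, power at f = 10% stays at 76.9%.

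**The gap is within ordinary planning uncertainty.** True rates of 9% and 6% would give 77.1% at 1125 per group. That argues for modest severity. It does not reconcile the two sections.

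**Conclusion.** The inconsistency is real: the allowance treats women who never reach 6 cm as replaced, while the primary analysis counts them. By the plan's own reasoning the stated 80% is not reached in the intent-to-treat comparison. The shortfall is 2 to 3 points with the planned chi-square test, or 5 to 6 points if the continuity-corrected formula is carried through. Both figures assume 9–10% never reach 6 cm and carry 8% risk in both arms. At 10%, plain-test power runs from about 79% (4% risk) to about 73% (16% risk).

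A reader might infer that the trial is seriously underpowered, that its result would be biased, or that randomization must move closer to 6 cm. The documents support none of these. The endpoint, test, population and type I error are unaffected, the loss is moderate, and nothing requires a change in recruitment. This is a should-fix point: the mechanism is certain and the size conditional.

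**What to change.** Keep 2475 women and the intent-to-treat primary analysis. In the Power calculation section:

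1. State that the 80% (8% versus 5%) refers to women who reach 6 cm.
2. State the power in all randomized women: about 77–78% with the chi-square test, 74–75% with continuity correction, assuming 9–10% never reach 6 cm and 8% risk among them in both arms. Add the range over those two assumptions, and name the sample-size formula used.
3. Bring the Abstract and the Discussion's remark on power into line.

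Optionally, pre-specify a supplementary analysis of women who reach 6 cm, compared as randomized, with the proportion reaching 6 cm reported by arm. It differs from the planned per-protocol analysis, which selects on treatment received. It should carry a caution: the set is defined after randomization in an open-label trial, so known allocation could influence who enters it.

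The cost is a reworded paragraph, a slightly less favourable power figure and, if chosen, one extra analysis. Recruitment and the timing of randomization stay as they are.

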### Statistical analysis

#### Planned analysis

First, a descriptive analysis of the clinical characteristics of the patients at baseline will be performed. The analysis of the primary and secondary endpoints will be an intent-to-treat analysis. A per-protocol analysis, including only women who effectively received the allocated treatment will also be performed.

All tests will be bilateral with a significance level of 5%. Quantitative data will be expressed as mean ± standard deviation or median with interquartile range, and qualitative data as a percentage with a 95% confidence interval.

No interim analyses are planned in this protocol.

#### Analysis of the primary endpoint

The analysis of the primary endpoint will estimate the effect of discontinuous administration of oxytocin on neonatal morbidity defined by a composite variable. All women included and randomized in the study will be included in the analysis which will be an intent-to-treat analysis. The percentage of neonates with morbidity using the composite criteria will be compared between the two groups: discontinuous oxytocin or continuous oxytocin by a chi-square test.

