### Setting

In 20 maternity units, in 15 cities in France.

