### Oxytocin infusion protocol and randomization

During the latent phase, oxytocin is administered according to national guidelines, i.e. low dose oxytocin infusion of less than 4 mUI/min with increments every 30 min, without exceeding a 20 mUI/min flow rate [9].

Women are included and randomized in two groups before 6 cm, during the latent phase (Supplementary Material 1):
The experimental group corresponds to discontinuation of oxytocin at the beginning of the active phase of the 1st stage of labor, i.e. oxytocin infusion is stopped beyond a cervical dilation equal or greater than 6 cm. In the experimental group, oxytocin can be re-started, if necessary, after 2 h of labor arrest (no progression of the cervical dilation and no progression of the fetal head).The control group corresponds to the standard care in France, i.e. when oxytocin is started during the latent phase of the 1st stage administration of oxytocin is continued during the active 1st stage and during the 2nd stage if the fetal heart rate is reassuring. As in French standard practice, the oxytocin infusion is maintained with no increments if cervical dilation progresses. If needed (abnormal fetal heart rate, uterine hyperstimulation) the infusion can be stopped.

The randomization is computerized and accessible 24 h on line. Subjects are distributed between the two groups at a ratio of 1:1. The randomization is stratified on the center and parity (nullipara/multipara). The stratification by center will allow considering the possible variations of practices between centers during labor or delivery (e.g. modalities of epidural analgesia, type of analgesic products used, etc.). Specific information on the practices is also collected in the electronic case report form (e-CRF). The stratification by parity is needed because multiparous and nulliparous women differ on several secondary endpoints such as duration of labor and mode of delivery.

Among women included in the STOPOXY trial, some will have a spontaneous labor and others an induction of labor including induction by oxytocin only or cervical ripening. Induction protocols and particularly cervical ripening methods (Prostaglandins E1, Prostaglandins E2, and mechanical methods) could differ between centers but this potential difference will be taken into account by the stratification by center.

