#### Subgroup analysis

We plan two subgroup analyses. The first analysis will be done according to the mode of onset of labor: cervical ripening, oxytocin, spontaneous. And the second analysis will be done according to parity.

The center and parity are two criteria used to stratify our randomization. They will therefore be distributed equally among the 20 centers. These two criteria are known to be associated with the use of oxytocin and labor duration which can both play a role on our primary endpoint.

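### Randomization is stratified by center and parity, but the primary test is an unstratified chi-square: valid, but it leaves a small amount of precision unused

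*Protocol article*

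**What the plan says.** - **Randomization.** Protocol article, Oxytocin infusion protocol and randomization: "The randomization is stratified on the center and parity (nullipara/multipara"). Setting: "In 20 maternity units, in 15 cities in France". Twenty units by two parity levels gives 40 strata.
- **Purpose of stratifying.** The same randomization section says "The stratification by center will allow considering the possible variations of practices between centers during labor or delivery". On induction and ripening methods that vary by center, it says "this potential difference will be taken into account by the stratification by center". It explains the parity factor by differences in secondary endpoints, naming labor duration and mode of delivery.
- **Relevance to the primary endpoint.** Subgroup analysis says of center and parity, in a sentence about the primary endpoint: "These two criteria are known to be associated with the use of oxytocin and labor duration which can both play a role on our primary".
- **Primary test.** Analysis of the primary endpoint compares the percentages between "discontinuous oxytocin or continuous oxytocin by a chi-square test". The abstract agrees: "The primary outcome will be compared between the two groups using a chi-square test with a *p*-value of 0.05".
- **Elsewhere.** Analysis of the secondary endpoints lists t, Wilcoxon, chi-square and Fisher tests. Parity returns only as a subgroup factor, and center enters no stated analysis.

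**The concern.** Stratified allocation makes the arms alike in center and parity. It does not by itself bring those factors into the test. If the strata differ in risk, the pooled chi-square counts the variation between strata as random error, although the design has already removed that variation from the comparison of the arms. The variance identity shows this. With p_s the risk in stratum s and p the overall risk,

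p(1 − p) = average of p_s(1 − p_s) + Var(p_s).

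The pooled test uses the left side, whereas a stratified test uses only the first term on the right. If Var(p_s) is zero the two tests agree. If it is positive, the pooled standard error is somewhat too large.

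At stake is a little power, and a mismatch between the design and the analysis. The protocol gives its own reasons for regarding the factors as relevant and then names a test that does not use them. Because the article names the primary test, this is a choice already made and not a detail left to an analysis plan.

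**Working it through.** **1. The plan's own figure.** Inputs from Power calculation: 8% versus 5%, two-sided alpha 5%, power 80%. With mean risk 0.065 and difference 0.03:

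n = [1.960·√(2·0.065·0.935) + 0.842·√(0.08·0.92 + 0.05·0.95)]² / 0.03² = 1059 per group.

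With the continuity correction, n' = (n/4)·[1 + √(1 + 4/(n·0.03))]² = 1125 per group, which is the stated figure. Then 2 × 1125 × 1.10 = 2475, also as stated. The ordinary chi-square without continuity correction has power 82.3% at 1125 per group and 85.7% at 2475 in total.

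**2. Stratum size.** 2475/40 ≈ 62 women per stratum. At an average risk of 6.5%, that is about 4 events.

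**3. Comparison of the two tests.** Allocation was simulated as balanced 1:1 within 40 strata, with 100,000 runs per setting. The pooled Pearson chi-square was compared with the Cochran-Mantel-Haenszel (CMH) statistic

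Z = Σ(x₁ₛ − n₁ₛtₛ/nₛ) / √Σ[n₁ₛn₀ₛtₛ(nₛ − tₛ)/(nₛ²(nₛ − 1))],

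where x₁ₛ is the events in one arm, tₛ the events in both arms, n₁ₛ and n₀ₛ the arm sizes and nₛ the stratum size.

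The following are assumptions, because the documents do not give them: the SD of center effects on the logit scale, the parity odds ratio, 55% nulliparae, and unequal centers with the largest three times the smallest. Overall risks were held at 8% and 5% for power, and at 8% in both arms for size.

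| N | Center SD / parity OR | Size, chi-square | Size, CMH | Power, chi-square | Power, CMH | Gain (points) |
|---|---|---|---|---|---|---|
| 2475 | 0 / 1.0 | 5.00% | 4.99% | 86.0% | 86.0% | 0.0 |
| 2475 | 0.3 / 1.5 | 4.97% | 5.10% | 86.2% | 86.4% | 0.2 |
| 2475 | 0.5 / 2.0 | 4.62% | 4.99% | 86.3% | 86.8% | 0.5 |
| 2475 | 0.8 / 3.0 | 4.13% | 4.89% | 86.7% | 88.1% | 1.3 |
| 2250 | 0 / 1.0 | 5.00% | 5.02% | 82.9% | 82.8% | 0.0 |
| 2250 | 0.3 / 1.5 | 4.92% | 5.02% | 82.8% | 83.0% | 0.2 |
| 2250 | 0.5 / 2.0 | 4.58% | 4.91% | 82.9% | 83.6% | 0.6 |
| 2250 | 0.8 / 3.0 | 4.23% | 5.08% | 83.6% | 85.1% | 1.5 |

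Gains are taken from unrounded powers. The Monte Carlo standard error of a 5% size is √(0.05·0.95/100,000) ≈ 0.07 points. A separate simulation with 20,000 runs per setting gave the same picture: chi-square size 4.9% down to 4.3%, CMH 4.8% to 5.1%, and a gain of 0 to about 1.1 points.

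**4. Reading the extreme row.** A size of 4.13% corresponds to a critical value of about 2.04, so the standard error is overstated by 2.04/1.96, or about 4%. That setting implies control risks from 0.6% to 32.4% across strata, which is a wide spread. In the mild setting (3.4% to 15.2%) the effect on size is close to nil.

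**The case against.** **The protocol's remark about stratification may be a statement about design.** Balanced allocation within centers means that center practices do not confound the comparison, and that is true without center in the model. The link to the primary endpoint is also indirect, through oxytocin use and labor duration, and is worded as a possibility. This stands: there is no outright contradiction. What remains is that factors the protocol calls relevant go unused in the primary test.

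**The consequence is small and on the safe side.** This stands in full. The loss depends on heterogeneity that the documents do not report, and it vanishes if the strata have similar risks.

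A reader might infer more than the documents support:
- *That the test is invalid or inflates false positives.* It does neither. Its size is at or below 5%.
- *That the trial falls below 80% power because of the test.* At the stated 8% versus 5% it does not. Power near 77% appears only if the experimental risk is diluted to 0.9 × 5% + 0.1 × 8% = 5.3%, to allow for women who never reach 6 cm. That is a separate question from the choice of test.
- *That the loss is larger for labor duration or cesarean delivery.* The documents give no figures from which to compute this, and the section on secondary endpoints is written in general terms.
- *That no effect measure is planned.* The section says that the effect will be estimated, and an article may leave the choice of measure to the analysis plan.

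**Changing a named primary test in a running open-label trial is not trivial.** Recruitment began in January 2020. This bears on the timing and documentation of the change, not on its merit.

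**Conclusion.** The point holds as a modest loss of efficiency and a mismatch between randomization and primary analysis. It is not an error of validity. Over the assumed range, the chi-square's true size is about 5.0% down to 4.1%. It gives up 0 to 1.3 points of power at 2475 women and 0 to 1.5 points at 2250. Planned power is kept and the sample size needs no change. These figures rest on the assumed center and parity variation, the assumed center sizes and parity mix, and a common odds ratio across strata. The improvement is worth making because both factors are already recorded at randomization.

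**What to change.** Amend Analysis of the primary endpoint, and the matching sentence in the abstract, as follows:

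1. The primary test is a Cochran-Mantel-Haenszel test stratified by center and parity. It is reported with the matching stratified risk difference or risk ratio and its 95% confidence interval.
2. The crude chi-square is kept as a sensitivity analysis.
3. If a regression is preferred, take parity as a fixed effect and center as a random effect. About 4 events per stratum is too sparse for 40 fixed stratum effects.
4. Date and document the change before any outcome data are examined by arm.

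The same adjustment is reasonable for secondary endpoints, above all labor duration and mode of delivery, which the protocol gives as its reason for stratifying by parity. No size of gain is claimed there.

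**Cost.** This is a change of analysis wording, with no new data and no new sample size. In a trial already recruiting, it is an amendment to the named primary analysis and should be recorded as one. The small statistical downside is that very small strata contribute little. Under the assumed center sizes, the smallest stratum would hold about 0.025 × 0.45 × 2475 ≈ 28 women and about 2 events (28 × 0.065 ≈ 1.8).
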